#### Secondary (clinical) outcomes

The following will be the outcomes for our definitive trial. Pain control and opioid analgesics are interlinked outcomes [43]. Recent studies have highlighted the need to consider both opioid use and pain control as patient-important, and the need to evaluate pain and opioid use trajectories [39, 44]. Hence, our primary outcome for the definitive trial will be to assess the effect of the multicomponent pain management pathway on ‘opioid free pain control’ at 8 weeks after TKA; defined as three or more consecutive days of < 4/10 average pain score on a 0–10 NRS with no opioid use for the operated knee. Secondary outcomes will include presence of CPSP, intensity of resting and movement evoked pain, POU, satisfaction with pain control, quality of life and complication rates. These outcomes will be collected at 3, 6, 9 and 12 months. Selection of our clinical outcomes was guided by the core outcome set developed by Wylde et al. [45] with some modifications. We also considered the need to evaluate outcomes that are patient important. As suggested by Wylde et al., we measure patient reported pain intensity both at rest and with movement. Assessment of CPSP has been considered based on international association for the study of pain definition (IASP) definition, which has been adapted in the International Classification of Diseases-11 version [46]. For evaluating functions, we use the Oxford Knee Score (OKS), which is a 12-item joint-specific questionnaire designed to assess pain and functional limitations in patients undergoing TKA. In a study of 505 patients undergoing primary TKA, OKS showed a good correlation with improvements in OKS in relation to pain (*r* = 0.56; *p* < 0.001) and physician function *r* = 0.56; *p* < 0.001) [47]. EQ-5D is a validated and commonly used tool developed by the EurQol group to measure quality of life. In a study of 758 patients with hip or knee OA, EuroQol (EQ-5D-5L) showed good reliability and internal consistency (Cronbach's alpha was 0.86) along with strong correlation with Western Ontario and McMaster Universities Osteoarthritis Index (WOMAC) pain and function scores (− 0.688 and − 0.782) [48]. To inform the future health economic evaluation of the main trial we will also capture information on the costs of providing the intervention, healthcare resource use, and productivity at 3, 6, 9 and 12 months post-operatively.

#### Measurement of clinical outcomes and economic

Opioid free pain control: For both groups, we will use a daily electronic diary to capture pain scores and opioid use between 1–6 weeks pre-op (to familiarize the patient on the use of the diary) and 8 weeks post-op. We will identify the number of patients achieving opioid-free pain control (defined in previous paragraph) in the intervention and control groups. We have partnered with ManagingLife Inc., who will provide the ManageMyPain app to capture daily pain scores and opioid use. This application is easy to use and secure. It is both Health Insurance Portability and Accountability (HIPPA) and Personal Information Protection and Electronic Documents Act (PIPEDA) compliant and has been recognised by Ontario Health Network (OTN) as an approved platform. This app has been used in previous studies to track pain resolution in surgical patients. Our surgeons estimate that 75% of their patients have a smartphone. For the approximately 25% who do not, we have access to donated smartphones to be used for research purposes. Alternatively for patients who cannot use MMP, a paper diary will be used.

We will measure the presence of CPSP as defined as per the International Classification of Diseases version-11 (ICD-11) [49].

We will measure CPSP Pain Intensity at Rest and during movement using the 0–10 Numerical Rating Scale (NRS).

We will measure persistent opioid use (POU) as a binary outcome as defined as the presence of daily opioid use, started after surgery or increased after surgery.

Using a 0 to 100 scale (0 = extremely dissatisfied, 100 = extremely satisfied), we will measure satisfaction with pain control.

We will assess return to function using the 5-item Return To Function (RTF) questionnaire developed at McMaster University to assess the ability to return to work, home and leisure activities. The RTF questionnaire has been used previously in orthopaedic trials, including an FDA-regulated orthopaedic device trial [50], to determine when a trial participant returns to work, leisure and activities around the home after an injury or surgery.

Using the 12-item Oxford Knee Score, we will assess improvement in knee function and pain following total knee replacement [51].

We will assess health-related quality of life using the Euro-QoL 5 Dimensions instrument consisting of 5 dimensions, including mobility, self-care, usual activities, pain/ discomfort and anxiety/ depression, which contains five levels of answers per dimension [52].

We will collect intervention costs and healthcare resource utilization information (e.g. hospitalization, physician visits) as well as information on productivity (e.g. time missed from work) using a self-administered questionnaire, which we developed for the purpose of this study based on our previous work [53].

We will also collect any surgery-related and knee-related adverse events (AEs), pain medication related adverse events, readmissions and serious adverse events (SAEs). We do not anticipate many risks to study participants beyond usual care. We provide education about safe opioid use and disposal and recognize the potential for opioid withdrawal if opioids are tapered too rapidly. Postoperative prescriptions will be structured and any reduction to chronic opioid use will be monitored, and our pain physicians will develop a structured set of operating procedures to minimize this risk, both preoperatively and postoperatively. Most importantly, the approach throughout the trial will be one of participant engagement and shared decision making. Any patients experiencing AE or SAEs will receive the necessary care at their institution.

### Randomization

The unit of randomization will be individual participants. We will use a 1:1 allocation ratio, stratified by site, with random block sizes of 2 and 4. Randomization will be completed by research personnel, 1–6 weeks before surgery to allow time for the pre-operative education interventions. We will use a centralized online randomization system integrated into REDCap to ensure allocation concealment. A statistician not otherwise associated with the trial will generate the randomization sequence.

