### Patient selection

All patients who are being scheduled for primary elective TKA will be screened for eligibility by participating surgeons (target approximately 1–6 weeks before surgery). We will aim to include proportions of men and women in our trial that are representative of the TKA population. We will record numbers of ineligible patients and those who decline to participate. The surgeon or their delegate will inform potentially eligible patients by phone or in person to invite them to speak with the research coordinator about the trial. Each institution will determine their own recruitment processes based on local research ethics board (REB)-approved practices. Sites will be allowed to select an informed consent method that meets their REB and local institutional guidelines. This could include written informed consent or verbal consent. The informed consent process will be documented in all cases.

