### Protecting against sources of bias

#### Blinding

Due to the nature of the study interventions, participants and the health care team cannot be blinded. We will have an independent blinded surgeon to evaluate each adverse event to minimize the risk of bias for that outcome. The primary study outcome of non-opioid pain control will be collected using a daily e-diary up to 8 weeks. Other study outcomes will be collected by research personnel not involved in the participants’ clinical care. Data analysts will be blinded for all outcomes.

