#### Minimizing contamination and co-interventions

Since the existing standard of care does not involve the coordinator or any component of interventions, there is minimal risk of contamination. Patients are allowed to receive other interventions outside of the study, but the role of a pain management coordinator currently does not exist outside of our study. Alternatively, there is a risk if patients are randomised to intervention but do not ultimately receive it. To minimize the risk of crossover, all efforts will be taken to maintain communication between the research personnel and the pain management coordinator. We will also hold weekly team meetings to provide updates on all patients. Participants who are receiving two joint replacements during the study period will only be included for one of their surgeries.

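### Site-stratified blocks of only 2 and 4 in an open-label trial make allocations easy to predict, an avoidable risk of selective enrolment that central concealment does not remove

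*Protocol article*

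**What the plan says.** The Randomization section fixes the scheme: "We will use a 1:1 allocation ratio, stratified by site, with random block sizes of 2 and 4". An independent statistician generates the sequence. The section then gives the safeguard: "We will use a centralized online randomization system integrated into REDCap to ensure allocation concealment". On who randomises and when, it says: "Randomization will be completed by research personnel, 1–6 weeks before surgery to allow time for the pre-operative education interventions".

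Under Blinding: "Due to the nature of the study interventions, participants and the health care team cannot be blinded". Only the intervention arm has a pain management coordinator, so past allocations are also visible in practice.

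Under Patient selection, screening lies with surgeons: "All patients who are being scheduled for primary elective TKA will be screened for eligibility by participating surgeons". The first approach is also made by the surgeon or someone acting for the surgeon, who refers interested patients to the research coordinator. Under Minimizing contamination and co-interventions, research personnel are to keep in contact with the coordinator, and: "We will also hold weekly team meetings to provide updates on all patients".

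The article does not give the proportions in which the two sizes are used, does not say whether site staff are told the sizes, and names no safeguard against inferring the next allocation from earlier ones.

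**The concern.** Allocation concealment has two parts: nobody can see the next entry on the list, and nobody can work it out. The central system provides the first. The second depends on the block scheme and on who knows earlier allocations. Here the lists are separate by site, the blocks are very short, the sizes are in print, and earlier allocations are open to the people running the trial locally. Varying between 2 and 4 helps little, because a block of 2 is fully determined once its first patient is placed.

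Someone who expects a particular arm next can, even without intent, bring a patient forward or hold one back. The most plausible route is the research personnel, who perform the randomisation and know earlier allocations.

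What could be biased are the comparative clinical results under Primary analysis: the hazard ratio for opioid-free pain control and the clinical estimates by group. The Overview of the design also allows pilot patients to enter the definitive trial, on condition that its methods do not change materially. If that condition is met, any selection in the pilot goes into the confirmatory data.

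**Working it through.** The article states no predictability figure, so there is none to reproduce.

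**Inputs**
- 1:1, by site, blocks of 2 and 4: Randomization.
- Three sites (Overview of the design) and 100 patients (Sample size determination): 100/3, about 33 per site if evenly spread (assumption).
- q, the probability that a block has size 2: not stated. Assumed 1/2; range 1/3 to 2/3 shown.
- The guesser knows all earlier allocations at the site and names the arm that is behind. A tie counts as 1/2.

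**Even-numbered patients.** Both sizes are even, so every block starts at an odd position and the arms are never equal before an even position. The guess is right with probability 1 at the second place of a block of 2. In a block of 4 it is right with probability 2/3 at the second place (two of the three remaining entries belong to the other arm) and 1 at the fourth. Hence

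P(even) = [q + (1 − q)(2/3 + 1)] / [q + 2(1 − q)]

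- q = 1/2: (1/2 + 5/6)/(3/2) = 8/9 = 88.9%
- q = 1/3: 13/15 = 86.7%
- q = 2/3: 11/12 = 91.7%
- limits: 5/6 = 83.3% (only 4s) and 100% (only 2s)

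The 89% is an average. With q = 1/2 the second patient at a site is guessed with 83.3%, the fourth with 91.7%, the sixth with 87.5% and the eighth with 89.6%.

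**Odd-numbered patients.** The first place of any block is a tie, 1/2. The third place of a block of 4 follows a 1–1 split with probability 2/3 (guess 1/2) or a 2–0 split with probability 1/3 (guess 1): 2/3 × 1/2 + 1/3 × 1 = 2/3. Hence

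P(odd) = [q/2 + (1 − q)(1/2 + 2/3)] / [q + 2(1 − q)] = (5/6)/(3/2) = 5/9 = 55.6% at q = 1/2.

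**All patients.** (8/9 + 5/9)/2 = 13/18 = 72.2%, against 50% for an unpredictable list.

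**Certain allocations.** A lead of two can arise only when a block of 4 opens with two equal entries (probability 1/3); the next two entries are then known. At q = 1/2 that is 1/2 × 1/3 × 2 = 1/3 certain allocations per block, over a mean block length of 3, so 1/9 = 11.1% in the long run.

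**Simulation and alternatives** (33 patients per site, block sizes used equally, same guesser, who also knows the scheme parameters)

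| Scheme | Even positions | All | Certain | Largest final site imbalance |
|---|---|---|---|---|
| Blocks 2, 4 | 88.6% | 71.5% | 10.7% | 1 |
| Blocks 4, 6, 8 | 75.6% | 67.2% | 2.4% | 3 |
| Big-stick, limit 3 | not computed | 57.4% | 14.8% | 3 |

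Check on the last row: under big-stick an allocation at the limit is certain and every other is 50:50. If c is the certain share, the guess rate is c + (1 − c)/2, so c = 2 × 0.574 − 1 = 0.148.

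**The case against.** The strongest case against this point concerns the consequence, not the arithmetic. The 89% needs someone who follows the whole site sequence in order and also influences who is randomised next. Surgeons or their delegates only invite patients to a conversation; consent follows, and research personnel randomise later, so an inviting surgeon may not know which place in the sequence a patient will take. The weekly meetings are described in connection with contact between research personnel and the coordinator, and the article does not say that recruiting surgeons attend. All patients being scheduled are to be screened, ineligible patients and decliners are counted, and eligibility is broad, which leaves little formal ground for turning a patient away. This stands as far as surgeons are concerned. It does not clear the research personnel, who hold both the knowledge and the timing.

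The stakes are limited. Adherence, recruitment and retention are judged against fixed thresholds without comparing arms, and the clinical results are descriptive and unpowered. Carry-over into the definitive trial is conditional. Pre-operative opioid use, knee function and EQ-5D are recorded in both arms at baseline, so selection on those could be seen and adjusted for; selection on unrecorded factors could not. All of this stands and lowers the weight of the point.

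A reader might infer that concealment has failed, that selective enrolment will take place, or that the feasibility verdict is compromised. The document supports none of these. It shows a predictable scheme and an open-label setting, not that anyone acts on them. A reader might also take 89% to apply to every allocation; it applies to even-numbered ones on average, and the figure for all is 72%. Nor does publication of the sizes in a journal article establish that site staff were told them.

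**Conclusion.** The point holds as an avoidable design risk. Central REDCap randomisation does not prevent inference from past allocations, and blocks of 2 and 4 within site make that inference easy: about 89% at even positions, about 72% overall and roughly 10 to 11% certain. These figures rest on equal use of the two sizes and on a guesser who tracks the full site sequence. The conclusion does not depend on the mix: the even-position figure is 87 to 92% over the plausible range and 83% even with no block of 2.

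The size of any resulting bias cannot be derived from the document. The risk applies to the between-arm clinical estimates and, conditionally, to the definitive trial; it does not apply to the non-comparative feasibility outcomes. It should be corrected because the remedy is nearly free, not because harm has been shown.

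**What to change.** In the Randomization section, replace "random block sizes of 2 and 4" with randomly varying blocks that exclude size 2, for example 4, 6 and 8. The independent statistician already named should generate the new site-stratified list for all patients still to be randomised. State that the new sizes are withheld from site staff until enrolment closes; this helps only with a new scheme, since 2 and 4 are already public. If patients have already been randomised under the present scheme, report baseline pre-operative opioid use by arm as a check for selection.

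The cost is one amended sentence and a new allocation table in the existing system. Balance is slightly looser: a final site imbalance of up to about 3 instead of 1 in simulation. The gain is real but partial: 89% falls to about 76% at even positions, 72% to about 67% overall, and certain allocations fall to 2 to 3%.

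A big-stick list with a limit of 3 per site is an alternative with a lower overall guess rate, about 57%. However, about 15% of its allocations are certain to anyone who knows the limit, more than under the present scheme, so it is suitable only if the limit is kept concealed.

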### Study follow-up

Participants will be followed from the time of their study inclusion (1–6 weeks pre-surgery) to 12 months after surgery. We will collect baseline data before surgery. We will collect daily pain scores using an electronic diary up to 8 weeks after surgery, and we will collect post-operative outcomes at 3, 6, 9 and 12 months after surgery (Table 3).

**Table 3 Tab3:** Schedule of EVENTS

Study event	Pre-op 1–6 weeks	In hospital	Postoperative weeks						Months			
			**1**	**2**	**3**	**4**	**6**	**8**	**3**	**6**	**9**	**12**
Screen and consent	X											
Identify high risk patients	I											
Pain education	I											
CBS intervention	I											
Electronic pain and opioid diary	X	X	X	X	X	X	X	X				
Check in with coordinator	I	I	I	I	I	I	I	I				
CPSP assessment^39^, and pain intensity with rest and movement									X	X	X	X
Opioid use	X	X						X	X	X	X	X
Satisfaction with pain control									X	X	X	X
Return to function									X	X	X	X
Knee function	X								X	X	X	X
EQ-5D	X								X	X	X	X
Health economics									X	X	X	X
Complications	X	X	X	X	X	X	X	X	X	X	X	X

*X* all groups, *I* intervention group only

### Protecting against sources of bias

#### Blinding

Due to the nature of the study interventions, participants and the health care team cannot be blinded. We will have an independent blinded surgeon to evaluate each adverse event to minimize the risk of bias for that outcome. The primary study outcome of non-opioid pain control will be collected using a daily e-diary up to 8 weeks. Other study outcomes will be collected by research personnel not involved in the participants’ clinical care. Data analysts will be blinded for all outcomes.

#### Minimizing contamination and co-interventions

Since the existing standard of care does not involve the coordinator or any component of interventions, there is minimal risk of contamination. Patients are allowed to receive other interventions outside of the study, but the role of a pain management coordinator currently does not exist outside of our study. Alternatively, there is a risk if patients are randomised to intervention but do not ultimately receive it. To minimize the risk of crossover, all efforts will be taken to maintain communication between the research personnel and the pain management coordinator. We will also hold weekly team meetings to provide updates on all patients. Participants who are receiving two joint replacements during the study period will only be included for one of their surgeries.

#### Minimizing expertise bias

The CBS sessions are based on the principles of CBT. Although no formal CBT training is required, we will employ pain management coordinators with some prior patient contact experience within the healthcare setting, and we will also develop a pain CBS ‘bootcamp’ to ensure pain management coordinators can successfully implement the CBS sessions, along with training for safe opioid weaning. We also have a pain psychologist within the study team to resolve any challenges relating to CBS sessions for specific participants.

Components of the intervention such as personalized prescriptions, pain management and support may also present expertise bias, as the pain management coordinator will be the participant’s first point of contact for all components. Therefore, to maintain consistency among sites, we will also engage the lead pain physician to liaise with each site to support the pain management coordinator in any decisions regarding pain management and prescriptions.

#### Minimizing attrition bias

Once a participant is enrolled in the trial, every reasonable effort will be made to follow the participant for the entire duration of the study period (12 months). Previously established orthopaedic-specific procedures developed and refined at our central coordination and methods centre will be implemented to improve participant retention. Our research group has consistently used and improved our participant retention strategies over the past 15 years and has published papers on minimizing loss to follow-up in orthopaedic trials [54]. In our group’s four most recent large trials, the loss to follow-up percentages were A-PREP trial–4% [55], HEALTH trial–14.9% [56], FLOW trial–10% [57], FAITH trial–9% [58]. Key strategies used to minimize loss to follow-up: aligning the follow up with standard of care visits; collecting more than one piece of contact information for the participant; research personnel will verify participants’ contact information at each visit and ask the participants their preferred form of contact; prioritizing outcomes if there is participant burden; and requesting permission to access medical records.

### Statistical methods

#### Sample size determination

This pilot trial is not powered to detect clinical differences, so we based our sample size on pilot trial sample size calculations using a confidence interval approach suggested by Thabane et al. [59]. We believe the study will be feasible if participant retention is 90% or greater and will consider > 80% retention acceptable with modifications. If 90/100 participants adhere to the study intervention, then the lower bound of the confidence interval will exclude 80% and we will consider the trial feasible. Therefore, we will include 100 participants in this pilot trial.

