### Study outcomes

#### Primary (feasibility) outcomes and criteria for success

Feasibility outcomes include intervention adherence, participant recruitment and participant retention (Table 1). We will note the percentage of participants receiving at least 3 of the 4 trial intervention components. We will consider > 90% as feasible; 80–90% to consider design modifications; and 80% as not feasible. Adherence to the intervention will be captured using an adherence checklist by the coordinator. The following criteria must be met to consider that the intervention components were adhered to for each patient: (1) patients must have reviewed both preoperative educational modules and 2 sessions of cognitive behavioural skills if in the high risk group; (2) coordinator must have stratified the patient into high or standard risk; (3) the surgeon must have provided a personalized discharge prescription, facilitated by the coordinator; and (4) the patient and coordinator must have connected in person or virtually for at least 6 of the 8 scheduled post-operative check-ins. We aim to recruit 100 patients in 4 months. We will consider > 90% participant retention to be feasible at 12 months post-operatively, 80–90% to consider design modifications and < 80% is not feasible. Table 2 shows the criteria for success of feasibility objectives.

**Table 1 Tab1:** Trial objectives, outcomes and analyses

***Feasibility objectives***	***Feasibility outcomes***	***Evaluation metrics***	***Analysis***
Intervention adherence	Percentage of patients receiving at least 3 of the 4 trial intervention components	> 90% feasible; 80–90% to consider design modifications; < 80% not feasible	Descriptive
Patient recruitment	Time to recruit target sample size	We aim to recruit 100 patients in 4 months	
Patient retention	Percentage of follow up at 12 months	> 90% feasible; 80–90%-consider design modifications; < 80%-not feasible	
***Clinical Objectives***	***Clinical outcomes***		***Analysis***
Opioid-free pain control	Time to three or more consecutive days of < 4/10 pain score on a 0–10 NRS with no opioid use for the operated knee		hazard ratios, 95% CI; Kaplan–Meier survival curve
Presence of chronic postsurgical pain (CPSP) at 3, 6, 9 and 12 months	Presence of CPSP as adopted in the International Classification of Diseases (ICD)-11 version by World Health Organization		descriptively as point estimates and 95% CI by group, with minimally important differences presented for context

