CPSP pain intensity at rest and movement	Average pain score over the previous week in 0–10 NRS		
Presence of persistent opioid use (POU)	Presence of daily opioid use, started after surgery or increased after surgery (binary)		
Satisfaction with pain control at 3, 6, 9 and 12 months	Using a 0 to 100 scale (0 = extremely dissatisfied, 100 = extremely satisfied)		
Return to function at 3, 6, 9, and 12 months	Using the Return to Function questionnaire		
Knee function at 3, 6, 9 and 12 months	Using Oxford Knee Scale (OKS)		
Quality of Life	Using Euro-Qol 5 Dimensions (EQ-5D) instrument		
Economic analysis	Intervention costs and healthcare resource utilization information as well as information on productivity (e.g. time missed from work) will be collected using a self-administered questionnaire, developed for the purpose of this study		QALYs associated with each study arm will be reported as point estimates along with confidence intervals but not compared in a formal economic evaluation
Complications	Surgery-related and knee-related adverse events, pain medication related adverse events, readmissions, and serious adverse events (SAEs)		descriptively by group

**Table 2 Tab2:** Feasibility criteria and determining success

Feasibility criterion	Proceed	Proceed with modifications	Do not proceed/major modifications
Adherence (at least 3 of 4 components)	> 90% of participants	80–90% of participants	< 80% of participants
Recruitment	100 participants in 4 months	100 participants in 4–12 months	< 100 recruited or > 12 months
Retention	> 90% of participants	80–90% of participants	< 80% of participants

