#### Primary analysis

Feasibility outcomes will be reported descriptively as numbers and percentages with 95% confidence intervals (CI). This pilot trial will not be powered to detect differences in clinical outcomes. Instead, we will report all clinical outcomes descriptively as point estimates and 95% CI, with minimally important differences presented for context, where available. We will also report hazard ratios for our primary outcome and time-to-event data graphically using a Kaplan–Meier survival curve. We will not impute for missing data in the pilot trial. All analyses will be conducted as intention-to-treat. We will prepare a full statistical analysis plan (SAP) for the definitive trial analysis.

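### The sample-size paragraph measures intervention adherence out of 100, although only about 50 participants can adhere, and its 90% boundary differs from the outcomes section and Tables 1 and 2

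*Protocol article*

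**What the plan says.** Under *Sample size determination*, the protocol article takes a confidence-interval approach. It begins with retention: "We believe the study will be feasible if participant retention is 90% or greater", with retention above 80% acceptable subject to modifications. The next sentence moves to adherence: "If 90/100 participants adhere to the study intervention, then the lower bound of the confidence interval will exclude 80" (per cent), in which case the trial will be considered feasible. It concludes: "Therefore, we will include 100 participants in this pilot trial".

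Under *Primary (feasibility) outcomes and criteria for success*, adherence is defined by component receipt: "We will note the percentage of participants receiving at least 3 of the 4 trial intervention components". More than 90% is feasible and 80–90% leads to considering design modifications. The same section takes more than 90% "participant retention to be feasible at 12 months post-operatively". Table 1 repeats these cut-offs. In Table 2 the row "Adherence (at least 3 of 4 components") and the retention row both place results above 90% under proceeding and 80–90% under proceeding with modifications.

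The *Randomization* section says: "We will use a 1:1 allocation ratio, stratified by site, with random block sizes of 2 and 4". Table 3 marks risk identification, pain education, the cognitive behavioural sessions and the coordinator check-ins as intervention group only. The *Control group* section describes usual care without a coordinator, and the section on contamination says that standard care contains no component of the intervention.

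Under *Primary analysis*: "Feasibility outcomes will be reported descriptively as numbers and percentages with 95% confidence intervals (CI").

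**The concern.** Adherence to the pathway has no meaning for a control participant, so its denominator is the intervention arm. The sentence that leads directly to the sample size nevertheless uses all randomised participants. Halving the denominator widens the interval, so the stated assurance that 80% is excluded at 90% adherence may no longer hold.

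A second problem lies in the same paragraph. It counts 90% as feasible, both for retention and through the 90/100 adherence example, while the outcomes section and both tables require strictly more than 90%. Exactly 90% is attainable for either outcome (45/50 for adherence, 90/100 for retention), so the document gives two classifications for one result.

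Adherence and retention are two of the three criteria that decide whether the definitive trial goes ahead. The rule at 90%, and the precision behind it, should be settled before the results are known.

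**Working it through.** **Inputs.** Total 100 (*Sample size determination*). Allocation 1:1 (*Randomization*), so about 100/2 = 50 in the intervention arm. Observed rate 90%, reference value 80% (*Sample size determination*). Confidence level 95% (*Primary analysis*), taken as two-sided. The article names no interval method, so several are shown.

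**Formulas**, with p = x/n and z = 1.96:
- Wald: p ± z·√(p(1−p)/n)
- Wilson: [p + z²/(2n) ± z·√(p(1−p)/n + z²/(4n²))] / (1 + z²/n)
- Exact (Clopper-Pearson): lower limit is the 2.5% quantile of Beta(x, n−x+1); upper limit is the 97.5% quantile of Beta(x+1, n−x)

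**Step 1: the plan's own figure, 90/100.**
- Wald: 0.90 ± 1.96·√(0.09/100) = 0.90 ± 0.059, or 84.1–95.9%
- Wilson: (0.9192 ± 0.0619)/1.0384, or 82.6–94.5%
- Exact: 82.4–95.1%

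All exclude 80%, so the statement reproduces when the denominator is 100.

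**Step 2: the same rate in the intervention arm, 45/50.**
- Wald: 0.90 ± 1.96·√(0.09/50) = 0.90 ± 0.083, or 81.7–98.3%
- Wilson: (0.9384 ± 0.0916)/1.0768, or 78.6–95.7%
- Exact: 78.2–96.7%
- Agresti-Coull: 78.2–96.1%; Jeffreys: 79.5–96.1%

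Of these two-sided intervals, only Wald excludes 80%. One-sided 95% lower bounds also exclude it (Wald 83.0%, Wilson 80.9%, exact 80.1%), but the analysis section points to ordinary 95% intervals.

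**Step 3: the smallest count out of 50 that excludes 80%.** For exact and Wilson it is 46/50 = 92% (exact 80.8–97.8%, Wilson 81.2–96.8%). For Wald it is 45/50.

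**Step 4: how often 80% would be excluded, if true adherence were 90%** (an assumption).
- Exact, n = 100 (needs at least 89): P(X ≥ 89) = 0.703
- Exact, n = 50 (needs at least 46): P(X ≥ 46) = 0.431
- Wald, n = 50 (needs at least 45): P(X ≥ 45) = 0.616

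**Step 5: the boundary at 90%.**

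| Result | Sample-size section | Outcomes section, Tables 1 and 2 |
|---|---|---|
| Adherence exactly 90% | feasible | modifications |
| Retention exactly 90% | feasible | modifications |

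If the true rate is 90%, P(exactly 90/100) = 0.132 for retention, and P(exactly 45/50) = 0.616 − 0.431 = 0.185 for adherence.

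**Step 6: do the two problems interact?** With 50 in the arm, the strict rule of more than 90% makes 46/50 the smallest count that proceeds, and Step 3 shows that this count excludes 80% by exact and Wilson. The lower bound is also above 80% by Wald (84.5%), Agresti-Coull (80.7%) and Jeffreys (82.1%).

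**The case against.** The strongest reply is that the adherence wording is a slip. The preceding sentence concerns retention, which is measured in all 100 participants, and for retention the 90/100 figure is correct and supports the sample size. That reading is plausible, and it stands to this extent: a reader might infer that the total of 100 has lost its justification, and the document does not support that. The text still says adherence, however, and on the retention reading it gives no precision for adherence at all. A correction is needed either way.

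Second, a reader might infer that the promised exclusion of 80% simply fails. That is too strong. The article names no interval, and the Wald interval at 45/50 does exclude 80%. Wald is a poor choice for a proportion near 1 in a sample of 50, but that is no evidence that the authors used something else. Leaving the method to an analysis plan is ordinary and is not itself a fault.

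Third, a reader might infer that the trial could proceed on adherence data that do not rule out 80%. The tabulated rules act on the observed percentage, not on a confidence limit. In an arm of 50 they send 45/50 to modifications and let 46/50 proceed, and 46/50 excludes 80%. The worry arises only if the looser sample-size wording overrides the tables.

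Finally, the two classifications of exactly 90% might be read as opposite verdicts. They are adjacent categories, and both proceed. The verdict of not proceeding begins below 80%.

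**Conclusion.** Two statements in the sample-size paragraph are wrong as written. The adherence scenario uses a denominator of 100 when about 50 applies. With the right denominator, the exact lower limit at 90% adherence falls from 82.4% to 78.2%, and the Wald half-width grows from 5.9 to 8.3 percentage points. Whether 80% is then excluded depends on the interval: not by two-sided exact, Wilson, Agresti-Coull or Jeffreys, but yes by Wald. The 90% boundary also conflicts with the outcomes section and Tables 1 and 2, for adherence and retention alike. This second point does not depend on the interval method.

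The sample size, the design and the tabulated decision rules are not invalidated.

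The figures assume two-sided 95% intervals and an intervention arm of exactly 50. Site-stratified blocks could leave the arm a little off 50, and the threshold counts would then shift. With 51 in the arm, for example, the smallest count above 90% is 46/51 = 90.2%, whose exact lower limit is 78.6%.

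**What to change.** Keep the total at 100 and change the wording as follows.

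1. **Adherence.** Use participants randomised to intervention (about 50) as the denominator. State, for example, that 45/50 gives about 78–97% and does not exclude 80% by the exact or Wilson interval, whereas 46/50 gives an exact interval of 80.8–97.8% and does. Label the figure with its interval, because the claim of exclusion turns on it.
2. **Retention.** Attach the 90/100 statement (about 82–95%) to retention, with all 100 randomised as the denominator.
3. **Boundary.** Use one rule at 90%, either above 90% or at least 90%, in the sample-size section, the outcomes section and Tables 1 and 2. If the rule of above 90% is kept, the smallest adherence count that proceeds in an arm of 50 (46/50) excludes 80%, so this change agrees with the first.

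The cost is limited to wording, plus a stated adherence precision that is less favourable than the present text suggests.
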